# Combined therapy

1. Allowable concomitant therapy

The interventions in this study will mainly consist of telemonitoring, information provision, and health counseling. The program will not interfere with by other therapies, as it is important for patients to successfully continue their existing therapies in the home care setting. Therefore, any other concomitant therapies that the patient is taking outside of the program will be allowed.

1. Unacceptable concomitant therapy

There are no specific concomitant therapies that are not acceptable.

# Survey Schedule

|  | **Evaluation item** | **Survey schedule** | | |
| --- | --- | --- | --- | --- |
|  |  | **At enrollment**  **(Baseline)** | **12 weeks after enrollment** | **24 weeks after enrollment** |
| **Interview or medical record** | Basic patient information | ◯ |  |  |
|  | Occasional visits and readmissions in the past 12 weeks | ◯ | ◯ |  |
|  | Occasional doctor visits and readmissions in the past 24 weeks | ◯ |  | ○ |
| **Questionnaire** | SGRQ | ◯ | ◯ | ◯ |
|  | EQ-5D | ◯ | ◯ | ◯ |
|  | SCAQ | ◯ | ◯ | ◯ |
| **Objective assessment items** | Respiratory function test | ◯ | ◯ | ◯ |
|  | 6-min walk test | ◯ | ◯ | ◯ |
|  | Average number of steps, activity level |  | ◯ | ◯ |

# Research period

The research period will be from May 2017 (after approval by the Ethics Committee of Tohoku University Graduate School of Medicine) to March 2019.

# Adverse event assessment

# Obtaining information

1. If a serious adverse event/failure occurs, the investigator will take appropriate action and report it to the principal investigator at the research institution.
2. The principal investigator of the research institution confirms the following items to the research participant.

**Items to be Confirmed by the Principal Investigator to the Researcher.**

| 1) Name of adverse event/failure  2) Severity classification [1]  3) Severity [2], reason for judging as serious  4) Predictability (unknown/known) [3]  5) Causal relationship with the intervention (study drug/device)  6) History of the event/defect (date of onset, course, outcome, and others)  7) Information regarding the participant's identification (initials, age, and gender) |
| --- |

**Severity Classification [1].**

I judge according to the National Cancer Institute Common Terminology Criteria for Adverse Events (NCI CTCAE v4.0: <http://www.jcog.jp/doctor/tool/CTCAEv4J_20150310.pdf>). If there is no item that corresponds to the NCI CTCAE Classification, the judgment should be made with reference to the following: "Criteria for Classification of Severity of Adverse Events."

| **Severity classification (NCI CTCAE grade）** | **Criteria** |
| --- | --- |
| **Mild (Grade 1)** | No symptoms or mild symptoms. Clinical or laboratory findings only.  No treatment required. |
| **Moderate (Grade 2)** | Requires minimal/local/noninvasive treatment.  Age-appropriate limitation of activities of daily living (ADLs) other than personal care*. |
| **Severe (Grade 3)** | Severe or medically significant, but not immediately life-threatening.  Requires hospitalization or prolonged hospitalization. Inability to perform activities/behaviors. Limitation of ADLs**. |
| **Most severe (Grade 4)** | Life-threatening. Requires immediate medical attention. |
| **Death (Grade 5)** | Death due to adverse event. |

*Instrumental ADLs (ADLs other than personal care): Meal preparation, shopping for daily necessities and clothing, using the telephone, managing money, and others.

**Self-care ADLs: The patient is able to bathe, to dress/undress, eat, to use the toilet, and to take medications; patient is not bedridden.

**Definition of Serious Adverse Events [2].**

| 1) Causing death  2) Life-threatening  3) Requiring hospitalization or prolonged hospitalization for treatment  4) Permanent or significant disability or dysfunction  5) Resulting in congenital anomalies in offspring. |
| --- |

Hospitalization stipulated in the research protocol, hospitalization to perform a therapy or examination planned before the research (before obtaining consent) and during the research (scheduled surgery, examination, and others), and hospitalization for therapy or examination not associated with the adverse event (medical examination and others) will not be considered as serious adverse events.

**Definition of Predictability (Unknown/Known) [3].**

| **○Unpredictable (unknown)**  The occurrence of the event or trend of occurrence, such as the number and frequency of occurrences, as well as conditions of occurrence, cannot be predicted from the official documents (package inserts, papers, and others) related to the study drug/device in question.  **○Predictable (known)**  The occurrence of the event or trend of the number and frequency of occurrences, as well as conditions for occurrence, can be predicted from the official documents (same as above) related to the study drug/device in question. |
| --- |

# Description of adverse events

Since this study will be an informational and health counseling activity for patients, adverse events from the intervention are likely to be very minimal. However, since respiratory function and 6-min walk tests will be performed during the measurement of secondary endpoints, it is possible that minor adverse events such as temporary worsening of symptoms may occur during these tests. In the event of an adverse event, the attending physician should be notified immediately for necessary action. For all adverse events, the progress during the intervention should be described in a case report, including the name of the adverse event, its severity, the reason it was deemed serious, the date of onset, the date of outcome, the treatment, the outcome, and the causal relationship with the intervention.

# Response to serious adverse events/failures (including the scope of adverse events to be reported to the head of the research institution)

# Response to adverse events/failures

1. If an adverse event/failure occurs, the investigator will take appropriate measures to investigate the cause, paying attention to ensuring the safety of the research participants [2]. This study will include a 6-min walk test as an endpoint. Since the 6-min walk test in this study is an outpatient examination, we will set up a pre-established system with the physician in charge and outpatient nurses to enhance patient safety and to promptly provide appropriate medical care in the event of an exacerbation of respiratory failure. In addition, a system will be established such that the same response can be provided to the physicians in charge at the collaborating research facilities, and efforts will be made to ensure participant safety.
2. As much as possible, the investigators will continue to follow up and to confirm the outcome of any symptoms or abnormal fluctuations in laboratory test values until, in principle, the event disappears, the patient recovers to the pre-research state, or it is determined that the event is no longer a clinical problem.
3. If the investigators determine that follow-up is unnecessary, such as when an irreversible adverse event/failure develops, follow-up will be terminated at the end of the study for the research participant; moreover, the reason for determining that follow-up is unnecessary should be stated in the comments section of the case report form.

# Report to the head of the research institution and the principal investigator

1. The principal investigator of the research institution shall report the occurrence of a serious adverse event/failure to the head of the research institution within time limits from the time when he/she becomes aware of the occurrence, as shown in the following table. The report should be made using "(Form No. 9) Report on Serious Adverse Events", which is

downloaded for clinical research from: http://www.med.tohoku.ac.jp/public/rinri_d.html.

1. In the case of a multicenter collaborative study, the principal investigator of the research institution should report the occurrence of a serious adverse event/failure to the principal investigator (principal investigator) within time limits from the time when he/she becomes aware of the occurrence, as shown in the following table. The report shall be made using the "(Reference Form 1) Report on Serious Adverse Events."
2. If the principal investigator is in another institution, the response will follow the procedures of the concerned institution.

**Criteria and Deadlines for Reporting to the Head of the Research Institution and Principal Investigator**

|  | **Mild/Moderate/Severe (Grade 1/2/3)** | | | **Most severe (Grade 4)** | | **Death** | | **Other medically important conditions** |
| --- | --- | --- | --- | --- | --- | --- | --- | --- |
|  | **Predictable (known)** | **Unpredictable (unknown)** | | **Predictable (known)** | **Unpredictable (unknown)** | **Predictable (known)** | **Unpredictable (unknown)** |  |
|  | **Hospitalization (No / Yes)** | **Hospitalization (No)** | **Hospitalization (Yes)** |  |  |  |  |  |
| **Causal relationship exists** | Report not required | Report not required | First report: Within 10 days  Additional report: As and when necessary | Primary report: Within 72 days  Second report: within 7 days  Additional reports: As and when necessary | | | |  |
| **No causal relationship** | Report not required | Report not required | First report: Within 10 days*  Additional reports: As and when necessary* | Primary report: Within 72 days*  Second report: within 7 days*  Additional reports: As and when necessary* | | | |  |

*On treatment or within 30 days of last protocol treatment date only

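### The reporting table exempts some events that the protocol itself defines as serious, and so conflicts with the reporting duties around it

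*Protocol*

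**What the plan says.** *Definition of Serious Adverse Events* gives five separate criteria. The third is "Requiring hospitalization or prolonged hospitalization for treatment"; the fourth, standing on its own, is "Permanent or significant disability or dysfunction". Planned admissions, and admissions unrelated to the event, are excluded.

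*Severity Classification* describes Grade 3 as "Severe or medically significant, but not immediately life-threatening" and includes "Inability to perform activities/behaviors" and limits on self-care. Grade 4 is "Life-threatening. Requires immediate medical attention".

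*Report to the head of the research institution and the principal investigator* says that the site principal investigator "shall report the occurrence of a serious adverse event/failure to the head of the research institution within time limits" shown in the table that follows. In a multicentre study the same table governs the report to the overall principal investigator.

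In that table (*Criteria and Deadlines for Reporting to the Head of the Research Institution and Principal Investigator*), Grades 1 to 3 form one block, split by predictability and hospitalisation. The row for causally related events begins "Report not required | Report not required", and so does the row for unrelated events. The first cell is for predictable events with or without admission, the second for unpredictable events without admission. A third cell, for unpredictable events with admission, asks for a first report within 10 days.

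**The concern.** The duty is written in terms of seriousness, but the table that carries it out replaces seriousness by hospitalisation, and for predictable events disregards even that. An investigator who follows the table would send no dated report for some events that the definition calls serious, including a related, unexpected and disabling one. An investigator who follows the text above the table, or the multicentre section below it, would report the same event. Sites could act differently on the same facts, and the overall principal investigator could learn late of a harm tied to the programme or to the study tests.

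**Working it through.** No arithmetic beyond a count applies. The check maps the definition and the grades onto the table.

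**Step 1: the grade of a disabling event.** By the protocol's own scale, loss of function that does not threaten life is at most Grade 3, because Grade 4 is reserved for threat to life. This reads the Grade 3 descriptors (admission, inability, limited self-care) as alternatives. The scale is also a fallback: CTCAE v4.0 comes first, and its item-level grades are not in the document.

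**Step 2: every Grade 1 to 3 cell.** Causality, predictability and admission give 2 × 2 × 2 = 8 combinations:

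| Predictability | Admitted | Related | Unrelated |
|---|---|---|---|
| Predictable | No | none | none |
| Predictable | Yes | none | none |
| Unpredictable | No | none | none |
| Unpredictable | Yes | 10 days | 10 days* |

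*Only on treatment or within 30 days of the last protocol treatment.

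Six of eight need no report. All four combinations without admission are among the six.

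**Step 3: serious events that fall in an exempt cell.**
- *Serious only by disability, Grade 3 or lower, not admitted.* Exempt in every case, even when related and unpredictable. With admission, the unpredictable case has the 10-day limit; if life-threatening, it moves to the Grade 4 columns.
- *Predictable, Grade 1 to 3, admitted.* Serious by the hospitalisation criterion, and exempt even when related.
- *Serious only by congenital anomaly.* The same logic applies, but this has little practical weight in a counselling programme for patients on NPPV, whose mean age the protocol's background puts at 72.6 years.

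**Step 4: whether another section closes the gap.**
- *Obtaining information* sends any serious event to the site principal investigator. It gives no deadline and does not go beyond the site.
- *Reporting to collaborating institutions* requires a multicentre report to the sites, the head of the institution and the Ethics Committee. It has no filter by grade or admission, so it contradicts the exempt cells, and it gives no deadline. For an event at a collaborating site it also depends on the overall principal investigator having been told, and that step runs through the same table.
- *Report content and method of reporting to the head of the research institution* includes research-related adverse events in the progress report, without timing.
- *CRF preparation* places the form after the 24-week intervention, so it is no prompt substitute.

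**Step 5: the last column.** The column for other medically important conditions has no entry in either row of the text available here. The table was read from a PDF and merged or lost cells are possible, so nothing is concluded from the blank.

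**The case against.** A definition of seriousness may properly be wider than the set of events that carry a deadline. The parent section announces the scope of events to be reported, and the table is titled as criteria as well as deadlines, so it can be read as a scope rule. The exemption of predictable admissions may even be deliberate, since readmission for acute exacerbation is a primary endpoint. This is a fair reading of intent, but the protocol does not state it: the sentence introducing the table speaks of serious events without exception, and the multicentre section repeats the duty without exception.

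The last column may have been meant for exactly these events. That cannot be excluded. Even so, the exempt cells are explicit and would then need a cross-reference to it.

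Some stronger readings are tempting but not supported:
- A reader might infer that a disabling event never reaches the head of the institution, or that some seriousness criteria have no reporting route. The sections listed in the check provide routes. What they lack is a deadline and agreement with the table.
- A reader might picture harm in an unsupervised programme with 17 people exposed. The programme has daily monitoring and nurse contact. The 6-minute walk test is done by the researcher, with a physician and nurse response arranged beforehand, and in both arms, so all 34 planned participants are exposed to it.

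**Conclusion.** The conflict holds in a limited form. Four parts of the protocol (the definition, the duty to report, the table and the multicentre section) disagree on which serious events must be reported, and the table, followed as written, removes the deadline from two kinds of event that are serious by definition: non-admitted disabling events below Grade 4, and predictable Grade 1 to 3 events that require admission.

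This rests on grading by the protocol's own scale and on the table as it can be read here. The frequency cannot be derived from the document. Non-admitted disabling events are probably rare. Predictable admissions could be more common if exacerbation admissions are classed as predictable, which the protocol does not settle. No endpoint, estimate or analysis changes. It is a safety-reporting inconsistency that should be corrected because the correction is specific and cheap.

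**What to change.** Reconcile the definition, the duty, the table and the multicentre section in one of two ways:

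1. Let all Grade 1 to 3 columns, predictable as well as unpredictable, turn on whether the event meets any criterion of the protocol's own definition of seriousness, rather than on hospitalisation alone.
2. Keep the table's scope, but state in the section that introduces it which serious events are exempt and why (for example, admissions already counted as endpoint events, if that was the intention), and make *Reporting to collaborating institutions* agree.

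In either case, confirm what the column for other medically important conditions requires, and enter it.

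The cost is one table edit or a short paragraph, plus ethics notification. No new data are needed, since the reason for judging an event serious is already among the items to be confirmed and recorded. The first option adds probably a few reports, or more if exacerbation admissions are classed as predictable; the second adds few or none.

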
The web-based program in the tele-nursing system consists of a patient site and a researcher site. The tablet terminal at the patient site has (1) a screen for recording daily physical condition, (2) a screen for video calls, (3) a screen for SNS input, and (4) a screen for respiratory rehabilitation information. The researcher's site will have (1) a list of the participant's telemonitoring data and (2) a screen for inputting comments. The researcher can check the participant's daily records and output the changes over time on a summary sheet.

The intervention period will be 24 weeks, and the number of ad hoc visits and readmissions during the past 12 and 24 weeks (primary endpoints) will be examined by the researcher at enrollment, 12 weeks after enrollment, and 24 weeks after enrollment, using the electronic medical record. At enrollment and at regular outpatient visits 12 and 24 weeks after enrollment, researchers will conduct a questionnaire survey about daily life, and perform respiratory function and 6-minute walk tests. In addition, activity meters will be checked 12 and 24 weeks after enrollment to collect data on the average number of steps and patient activity. Respiratory function and 6-min walk tests at enrollment as well as 12 and 24 weeks after enrollment will be performed by the researcher using equipment purchased using the research fund, since these tests are not covered by insurance and are outside the scope of usual medical care. Since the primary endpoints of this study are the number of emergency visits and rehospitalizations due to acute exacerbations of chronic respiratory diseases, the intervention will not be stopped in the event of worsening symptoms due to acute exacerbations. If the participant dies, the intervention is terminated because the study cannot continue. If a participant requests that the intervention be continued after their participation in the program, the intervention may be offered for an extended period of time, regardless of whether the participant is in the intervention or control group.

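### For Grade 4 events and deaths, the reporting table makes the second report (7 days) due before the primary report (72 days), so the deadlines do not work as written

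*Protocol*

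**What the plan says.** The Protocol section *Report to the head of the research institution and the principal investigator* requires the principal investigator at the institution to report serious adverse events to the head of that institution. In a multicentre study the report also goes to the lead principal investigator. Both reports are due "within time limits from the time when he/she becomes aware of the occurrence, as shown in the following table".

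The table that follows, *Criteria and Deadlines for Reporting to the Head of the Research Institution and Principal Investigator*, has one row for causally related events and one for unrelated events. In each row a merged cell covers Grade 4 events and deaths, predictable or not. It reads "Primary report: Within 72 days" and then "Second report: within 7 days". The unrelated row repeats both figures with an asterisk, explained as "On treatment or within 30 days of last protocol treatment date only".

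For Grade 1-3 events the table asks for a report only when the event is unpredictable and involves hospitalization. There the limit is "First report: Within 10 days".

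**The concern.** A second report cannot sensibly be due before the first. The figure of 72 days also looks out of line with the 10 days allowed for a less severe class of event. The text is operative: the preceding section makes these limits the investigator's reporting duty, and the same figure appears in both causality rows.

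At stake is how quickly news of a death or life-threatening event reaches the head of the institution and the lead principal investigator. Other sections also call for reporting:

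- *Obtaining information*: from the investigator to the principal investigator at the institution.
- *Description of adverse events*: immediate notice to the attending physician, and a case report entry.
- *Reporting to collaborating institutions*: reports to the collaborating sites, the head of the institution and the Ethics Committee.
- *Report content and method of reporting to the head of the research institution*: adverse event status within the progress report.

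None of these sets a limit in days. The table is therefore the only timed rule for reporting these events to the head of the institution and the lead principal investigator, and for the most severe events it contradicts itself.

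**Working it through.** No sample size, power or error rate is involved. The check compares the stated deadlines on a common clock.

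**Inputs**

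| Input | Value | Source in the Protocol |
|---|---|---|
| Primary report, Grade 4 or death, both rows | 72 days | Deadlines table |
| Second report, same cells | 7 days | Deadlines table |
| First report, unpredictable Grade 1-3 with hospitalization, both rows | 10 days | Deadlines table |
| Start of the clock | awareness of the event | Section introducing the table |

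The Grade 4 and death cell says primary where the Grade 1-3 cell says first. Since a second report follows it, the primary report is read as the first.

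**Reading A: both limits run from awareness, as the introducing section states**

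- Primary report due by day 72; second report due by day 7.
- Gap: 72 − 7 = 65 days, with the second report due first.
- A site that keeps to the 7-day line has reported by day 7, and the 72-day limit then has no function.
- A site that takes the primary-report line as its first deadline works to day 72. The two lines of one cell thus point to first contact dates 65 days apart.

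**Reading B: the 7 days run from the primary report**

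- Primary report due by day 72; second report due by day 72 + 7 = 79 at the latest.
- The order is restored, but this departs from the stated clock.
- Against the 10-day limit, the first deadline for Grade 4 events and deaths is 72 − 10 = 62 days later, or 72 / 10 = 7.2 times as long.

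**Result**

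Reading A reverses the order of the two reports. Reading B gives the gravest class of event a far longer first deadline than a less grave class. Because the 72-day figure stands in both rows, a single damaged table cell does not explain it. No other section states a different limit that would settle the matter.

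**The case against.** The strongest reply is that this is a slip of one word or one figure, and that a careful site would be protected by the 7-day line. Part of that stands. On the stated clock the 7-day limit also binds, so a compliant site reports a death by day 7, earlier than the 10 days set for the Grade 1-3 class. But the site then has to disregard one of the two deadlines in the cell, and the table does not say which one governs.

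The reach of the table may also be limited. Where the principal investigator belongs to another institution, the introducing section defers to that institution's procedures, so not every site may be governed by this table. This narrows the effect without removing the contradiction.

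A reader might infer several stronger claims that the Protocol does not support:

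- **That a site may stay silent for 72 days after a death.** This ignores the 7-day line, or else requires counting it from the primary report.
- **That 72 days is 43% of the intervention and measures the harm.** The Protocol says "The intervention period will be 24 weeks", so the ratio is 72 / (24 × 7) = 72 / 168 = 43%. The deadline runs from awareness, however, and the intervention ends if the participant dies, so the ratio has no useful meaning.
- **That the rule ending the study at 10% intervention-related adverse events depends on this table.** The section on interim analysis and early termination does not make that link. The rule counts all related adverse events, and the table exempts many Grade 1-3 events from reporting.
- **That these events have no other reporting route.** Other routes exist; what they lack is a day limit.
- **That the unit is the error.** This is plausible, but the Protocol does not show the intended value.

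**Conclusion.** The point holds as an internal contradiction in an operative safety-reporting rule. For Grade 4 events and deaths, in both causality rows, the second report falls due 65 days before the primary report on the clock that the Protocol gives. The alternative clock avoids the reversal only by setting a first deadline 7.2 times as long as that for unpredictable Grade 1-3 events with hospitalization.

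The conclusion rests on two readings of the text: that the primary report is the first report, and that the introducing section's clock applies to every limit in the table. If the second is dropped, the mismatch with the 10-day limit remains. The finding does not show that any event would in practice be reported late, and it does not establish what the correct limit is. It should still be corrected, because no other timed rule for reporting deaths and life-threatening events to these recipients fills the gap.

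**What to change.** Reconcile the 72-day, 7-day and 10-day limits with each other in both causality rows, and state for each report when its clock starts, consistently with the section that introduces the table. Confirm the intended first-report limit for Grade 4 events and deaths against the institution's own serious adverse event reporting procedure. The Protocol alone does not supply that value, and none is proposed here.

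Issue the correction through the procedure in *Changes to the research protocol*, with Ethics Committee review and approval by the head of the institution. A memorandum will not do, because that section reserves memorandums for explanation that leaves the content unchanged. Sites should be alerted to the inconsistency while the correction is pending.

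The cost is one corrected table, its review and approval, and a notice to sites. The design, data collection and analysis are unaffected.
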